##### Compliance With Study Intervention in Both Study Groups

Adherence will be evaluated as follows:

(A) Intervention group:

Administration of the prescribed treatment will be monitored daily through visits on the hospital ward by the local study nurse.Treatment response will be monitored daily for a maximum of 30 days by the study physician and treatment will be adjusted accordingly.

(B) Control group (standard care):

Diagnostic evaluations, plasma sodium levels and prescribed treatment will be recorded by the local study nurse through evaluation of the patient-chart and laboratory values after patient is discharged from hospital.The study team will not contact or advise the attending physicians in any way.

### Follow-Up

All patients (or if they cannot be reached their general practitioner) will be contacted 31 days and 1 year after the initial hospitalization by a member of the local study team who was not involved during the hospitalization and who is blinded to the allocated treatment group.

The following will be evaluated in a standardized survey:

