### Screening and Recruitment

To enable a daily screening of all hospitalized patients, plasma sodium values ordered through regular care will be screened using an electronic alert system by the local study physician.

Patients will be contacted as soon as the diagnosis of hypotonic hyponatremia <130 mmol/l is established. Patients may be eligible for study participation at any time during their hospitalization.

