### Randomization

Participants will be randomly 1:1 assigned to either the targeted-sodium-correction group or the standard treatment group. Randomization will be performed by the online database system SecuTrial®, stratified by study site and using permuted block of random sizes. The allocation sequence will be implemented by the study data manager of the clinical trial unit Basel, Switzerland. Randomization will be done directly after inclusion of each patient in the online database system.

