
Episodes of overcorrection (defined as increase >12 mmol/l/24 h, respectively 18 mmol/l /48 h) and their complications will be recorded. Targeted plasma sodium correction will be maintained—for a maximum of 30 days—until normonatremia is achieved or when the patient is discharged from hospital. At discharge the last available plasma sodium level and whether or not patient was treated according to protocol will be recorded. Not treated according to protocol applies in the case treatment recommendation is not implemented or the patient does not adhere to the prescribed treatment (details see below “Compliance with study intervention”). In case of hospitalization exceeding 30 days, the last plasma sodium level before stopping the intervention (day 31) will be recorded as the discharge plasma sodium. Treatment after discharge will not be influenced by the study team, however a treatment recommendation and request to monitor plasma sodium levels will be given to the general practitioner in the discharge letter.

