**Primary outcomes:**

Survival status, date of death (if applicable)Rehospitalization since index hospitalization

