#### Primary Analysis

Analysis of the primary outcome will follow the intention-to-treat principle. It will be based on the full analysis set. To test whether the study intervention differs from standard care 30 days after randomization, the Pearson's χ^2^-test without Yates's correction will be applied. Threshold for rejecting the null hypothesis will be α = 5%. The estimated absolute difference between study arms will be reported alongside its 95% confidence interval.

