#### Secondary Analysis

Each of the components of the primary outcome, death and rehospitalization, will be analyzed separately as described for the primary outcome. Time to death and rehospitalization after 30 days and 1 year will be analyzed by fitting Cox proportional hazards regression models with trial arm as explanatory variable. Hazard ratios including their confidence intervals will be reported. Patients will be censored on their last known follow-up. To illustrate the course of deaths and re-hospitalizations in the two treatment arms, a Kaplan-Meier Curve will be presented.

Length of hospital stay will be calculated in days considering index and each rehospitalization separately and by the sum of all hospital stays. Standard summary statistics for numerical data will be performed. If distribution of data allows, significant differences of mean of length of hospital stay between arms will be assessed with a *t*-test (two-sided α = 5%). If distribution is skewed, data will be transformed or other models selected.

The secondary outcomes (falls, fractures, course of hyponatremia, recurrence of hyponatremia, severe symptomatic hyponatremia, overcorrection of hyponatremia) will be analyzed as described for the primary outcome. To account for multiple occurrences of falls, fractures, and recurrence of hyponatremia after 1 year, we will apply a Poisson model.

Diagnostic performance of biomarkers will be assessed by calculating sensitivity, specificity and accuracy as well as best cut-offs. Gold standard is the correct diagnosis of etiology of hyponatremia, which is expert opinion based on biochemistry results and treatment response.

Analyses of differences of quality of life score and of executive functioning score between arms will be performed also considering grade of hyponatremia and its correction. Multivariate linear models will be used to explore possible associations.

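### The contact that collects the 30-day primary outcome is timed from the index hospitalisation, while the analysis window runs from randomisation, and the two do not match.

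*Protocol article*

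**What the plan says.** **Analysis window.** Study Design places the primary outcome 30 days after inclusion. Primary Analysis has the same length and origin: "To test whether the study intervention differs from standard care 30 days after randomization". The Randomization section makes the two origins one moment: "Randomization will be done directly after inclusion of each patient in the online database system".

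**Collection.** Follow-Up times the contact differently: "All patients (or if they cannot be reached their general practitioner) will be contacted 31 days and 1 year after the initial hospitalization". The survey item for the larger component of the outcome reads "Rehospitalization since index hospitalization". No end date is attached to it. The article names a date for death in this list but none for readmission. The secondary list uses both origins: falls are counted over 30 days from randomisation, while fractures and recurrence are counted from the index hospitalisation.

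**Enrolment and stay.** Screening and Recruitment states: "Patients may be eligible for study participation at any time during their hospitalization". In the intervention arm, correction continues for at most 30 days "until normonatremia is achieved or when the patient is discharged from hospital". Longer stays are foreseen: "In case of hospitalization exceeding 30 days, the last plasma sodium level before stopping the intervention (day 31) will be recorded".

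**Length of stay.** Secondary Analysis treats it as a separate outcome: "Length of hospital stay will be calculated in days considering index and each rehospitalization separately and by the sum of all hospital stays".

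**The concern.** Two things are at stake, and they differ in how firmly the text supports them.

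First, the rule for collecting the primary outcome does not fit the window in which it is analysed. The article does not say whether the contact is counted from admission or from discharge, and neither reading gives a contact just after day 30 from randomisation. One reading can miss events inside the window. The other brings in events outside it, which must then be removed by date.

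Second, with randomisation as the origin, time still spent in the index stay is time in which rehospitalisation cannot occur. A patient whose index stay outlasts day 30 cannot have that event at all. If the arms differ in index stay, the rehospitalisation component moves for a reason unrelated to benefit. This component is the larger one (18.5% against 6.4% for death in the sample size section).

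**Working it through.** **1. The plan's own figure.** Planning rates are 23% and 18%, two-sided α 5%, power 80%, Pearson χ² without continuity correction.

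n per arm = [1.960·√(2·0.205·0.795) + 0.842·√(0.23·0.77 + 0.18·0.82)]² / 0.05² = 1,023 after rounding up, or 2,046 in total. The plan states 2,050 evaluable; 2,050 / 0.90 = 2,278. Power with 1,025 per arm is 80.1%. The sample size reproduces, and this point does not change it.

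**2. The two clocks side by side.** Let *a* be the days from admission to randomisation and *s* the days from randomisation to discharge.

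- Contact counted from admission falls on day 31 − *a* after randomisation. For *a* = 5 that is day 26, so the last four days of the window are not yet observed. Any *a* of 2 or more gives a contact before day 30.
- Contact counted from discharge falls on day 31 + *s*. For *s* = 5 to 12 that is day 36 to 43, so 6 to 13 days beyond the window are covered.

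The values of *a* and *s* are examples; the article gives none. The start of the survey item does little harm, because nobody can be readmitted before discharge. What matters is that the item has no end, so the window as collected closes whenever the contact takes place.

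**3. Effect of a difference in index stay.** Assumptions, none of them in the article:

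- constant rehospitalisation hazard after discharge;
- the 18.5% planning rate runs from randomisation (the article states no origin);
- control stay after randomisation *L* = 5, 8 or 12 days;
- no true treatment effect.

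Hazard: h = −ln(1 − 0.185) / (30 − L). Rehospitalisation with *k* extra index days: 1 − exp[−h·(30 − L − k)].

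| L (days) | h per day | drop, k = 1 | drop, k = 2 | drop, k = 3 |
|---|---|---|---|---|
| 5 | 0.00818 | 0.67 points | 1.34 | 2.03 |
| 8 | 0.00930 | 0.76 | 1.53 | 2.31 |
| 12 | 0.01136 | 0.93 | 1.87 | 2.83 |

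Two extra days would thus imitate 27 to 37% of the planned 5-point effect (1.34/5 to 1.87/5).

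**4. What that would do to the test.** Take 1,025 per arm and a control rate of 23%, and let the whole drop *d* pass into the composite. The chance of a significant result favouring the intervention is Φ[(d − 1.96·SE₀)/SE₁], with SE₀ the pooled and SE₁ the unpooled standard error. Against a nominal 2.5%, it is 5.5 to 7.3% for one extra day, 11 to 17% for two and 20 to 34% for three. With equal stays it stays at the nominal level. If the intervention shortens the stay, the shift goes against it.

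**The case against.** The strongest reply is that the analysis window itself is consistent. Study Design and Primary Analysis agree once inclusion and randomisation are one moment. Follow-Up sets when someone makes contact; it does not redefine the outcome. A late contact collects too much rather than too little, and surplus events can be cut at day 30. The planned Cox models for time to rehospitalisation, and the length of each rehospitalisation, could not be produced without readmission dates, so the dates are probably recorded. The article also refers the assessment schedule and the full outcome list to supplementary tables that are not shown.

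Most of this stands. A reader might infer that the primary outcome is analysed on two contradictory clocks; the text does not support that. The mismatch lies between analysis and collection. It remains a stated rule that does not fit, not an omitted detail, and the admission reading can lose events that no later cut restores.

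A reader might also infer that the intervention can win by prolonging the stay. No section says it does. Correction ends at discharge, decisions other than correcting sodium stay with the attending physicians, and the Discussion worries about early discharge instead. The size in the working is conditional on a difference in stay that the article does not document.

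Finally, stay is already reported by arm, so a difference would be visible. That is a partial answer: the comparison is not linked to the primary outcome, and an in-hospital death shortens the stay and so looks favourable.

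**Conclusion.** The collection rule for the primary outcome should be brought into line with its analysis window. This rests on the text alone and needs no assumption about length of stay.

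The dependence on index stay is a real property of the endpoint, but conditional: about 0.7 to 0.9 points per extra day in one arm, given a stay of 5 to 12 days after randomisation, a constant hazard after discharge, and an 18.5% rate that runs from randomisation. It touches only rehospitalisation; deaths in the index stay are counted in full.

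One tempting figure should not be used as a bias. Under the same assumptions, 18.5% from randomisation corresponds to 1 − exp(−30h) = 21.8 to 28.9% from discharge, about 3 to 10 points more. Setting this against the 5-point target would mislead: the change of clock moves the rate in both arms, whereas the target is a difference between them.

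**What to change.** - Set the 30-day contact at day 31 or later after randomisation.
- Word the survey item as rehospitalisation since randomisation, with the date of each readmission.
- State that only deaths and readmissions dated within 30 days of randomisation count towards the primary outcome.
- For patients already enrolled (750 of 2,278 when the article was written), confirm readmission dates from medical records.
- Add one supportive analysis: days alive and out of hospital to day 30 from randomisation, compared between arms and reported beside the primary result. It gives no credit for a longer index stay or for early death.
- Keep randomisation as the origin of the primary analysis. Any analysis from discharge should be descriptive only, because discharge happens after randomisation and in-hospital deaths would need separate handling.

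The cost is a change of wording, one date field in the survey, a check of records for earlier patients, and a small extra analysis on data already collected. Primary test and sample size are unchanged.

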**Primary outcomes:**

Survival status, date of death (if applicable)Rehospitalization since index hospitalization

**Secondary outcomes:**

Number of falls within 30 days since randomizationOccurrence of any medically confirmed fractures since index hospitalizationRecurrence rate of hyponatremia since index hospitalization. Additional data from the general practitioner or medical records will be checked to further validate this point, if indicatedComplications due to overcorrection of hyponatremia (i.e., osmotic demyelination according to MRI scan or neurological diagnosis)Mentioning of hyponatremia and its etiology in the discharge letter from the index hospitalization (30 day follow up only)Score of quality of life EQ-5D-5L Test (if applicable).

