1. **Diagnosis:**Diagnosis of hyponatremia will be made by the local study physician and will be reviewed by the local principal investigator. According to the *ECPG*, patients will be classified into the 3 main groups of hypotonic hyponatremia (decreased/normal/increased extracellular fluid volume; details see Supplementary Figure 1). If the diagnosis is uncertain, the most likely categorization will be chosen. This initial diagnosis can and shall be changed according to treatment response and/or additional clinical information. The final diagnosis will be made before the patient is discharged.2. **Treatment:**The proposed treatment recommendation will be based on the predefined algorithms which were developed in accordance to the ECPG(2) and the EPR(3) (details see Supplementary Figure 2). The treatment algorithm is a recommendation only, meaning the proposed algorithm is intended as a guideline rather than a strict treatment plan. This approach takes into account the sometimes limited data for certain treatments (36) and enables the local expert to decide upon the best treatment for every patient individually based on the available treatment options. Given that the hyponatremia patient population in clinical practice is very heterogeneous, we decided a tailored approach for hyponatremia correction would be in the best interest of the patients. Except for correction of hyponatremia, the local study team will not influence other treatment goals and decisions, which will be fully at the discretion of the attending physicians. Treatment response and adherence will be evaluated daily. The study nurse will report to the study physician, who will additionally examine the patient if clinically indicated. The study physician will then—under the supervision of the local principal investigator—adapt treatment recommendation according to the predefined treatment goals and inform the treating physicians about the treatment modification. The general treatment goal is to raise plasma sodium levels by at least 2 mmol/l/24 h. These treatment goals also define the time until the next treatment step should be implemented. The following management rules apply:increase ≥2 mmol/l/24 h and <12 mmol/l/24 h and 18 mmol/l/48 h: current treatment option will be maintained until plasma sodium level has normalizedincrease <2 mmol/l/24 h: treatment will be intensified or switched to a different modalityincrease >12 mmol/l/24 h and/or 18 mmol/l/48 h: treatment will be discontinued and, if needed, counter regulatory actions (i.e., hypotonic infusion, administration of desmopressin) will be administered according to the decision of the local principal investigator.

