### Sample Size Calculations and Statistical Analyses

#### Determination of Sample Size

Sample size was estimated based on our already completed observational multi-center study in 298 patients with profound hyponatremia (37, 38). The study showed a 30-day mortality rate of 6.4% and a 30-day rehospitalization rate of 18.5%. Of the re-hospitalized patients, ~2% died and thus were counted twice. We therefore propose a combined event rate of 23% under standard care. Our systematic review identified only one study that investigated the impact of targeted correction of hyponatremia on mortality and rehospitalization (25). In this observational study, an absolute reduction of the combined event rate of 7.1% (33.7 vs. 26.6%) was reported. Through our intervention, we expect to achieve an absolute risk reduction for mortality and rehospitalization of 5 %. Sample size was calculated for a Pearson's χ^2^-test. We set 80% power for a two- sided test with an α error of 5%. A drop-out rate of 10% was assumed. In order to have 2050 evaluable patients, 2,278 patients must be recruited.

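### The only stated between-arm analysis of quality of life and executive functioning takes in achieved sodium correction, a result of the treatment, so it does not estimate the effect of allocation

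*Protocol article*

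**What the plan says.** The Follow-Up section lists "Score of quality of life EQ-5D-5L Test (if applicable" among the secondary outcomes. On timing and source it says: "All patients (or if they cannot be reached their general practitioner) will be contacted 31 days and 1 year after the initial hospitalization".

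The last paragraph of Secondary Analysis covers quality of life and executive functioning together. The comparison "between arms will be performed also considering grade of hyponatremia and its correction", and then: "Multivariate linear models will be used to explore possible associations". An earlier paragraph of that section names the secondary outcomes that are handled like the primary one: falls, fractures and four sodium-related outcomes. Neither score is in that list.

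The Intervention Group section states what the treatment acts on: "The general treatment goal is to raise plasma sodium levels by at least 2 mmol/l/24 h". The Objectives section gives the secondary objective as finding out whether the intervention benefits other outcomes that matter to patients.

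**The concern.** The secondary objective is about the strategy as allocated. The comparison that answers it contrasts the randomized arms and adjusts, if at all, for variables fixed before randomization. Grade of hyponatremia at baseline is such a variable. Correction of hyponatremia is not: it is observed after randomization and is the direct target of the intervention.

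Holding correction fixed asks a different question, namely whether the arms differ among patients whose sodium rose equally. If the treatment helps by raising sodium, the expected answer is no difference, however large the benefit. Correction is also not randomized. Anything that affects both how far sodium rises and how the patient feels will bias the arm coefficient. At stake is whether these two secondary outcomes can show a benefit that the trial actually produces.

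**Working it through.** **Plan's own figure.** The article gives no effect size or precision for quality of life. Its one calculation is for the primary outcome, 23% against 18%, two-sided 5%, power 80%:

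n per arm = [1.960·√(2·0.205·0.795) + 0.842·√(0.23·0.77 + 0.18·0.82)]² / 0.05² = 1,023, or 2,046 in total (2,050 stated). 2,050/0.90 = 2,278. This reproduces and is not touched by the point.

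**Model for the check.** Let A be arm, M achieved correction in mmol/l, U an unmeasured prognostic factor (SD 1) and Y the utility score:

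- M = 5 + Δ·A + g·U + error, error SD 4
- Y = 0.70 + b·M + d·A + 0.05·U + error, error SD 0.2

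All of these values are assumptions. Δ is the arm difference in correction (2 or 4), b the utility gain per mmol/l (0.005 or 0.01), g the link between U and correction (0, 1 or 2), and d any effect not acting through sodium.

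**Formulas.**

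- Arm coefficient without M: b·Δ + d, the total effect of allocation.
- Coefficient of M given arm: b + 0.05·g/(g² + 16).
- Arm coefficient with M in the model: (b·Δ + d) − Δ·[b + 0.05·g/(g² + 16)] = d − Δ·0.05·g/(g² + 16).

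The term b·Δ cancels, so the adjusted coefficient carries no trace of a benefit that runs through sodium.

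**Results with d = 0** (simulated with N = 2,000,000):

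| g | Δ | True total effect | Adjusted, formula | Adjusted, simulated |
|---|---|---|---|---|
| 0 | 2 | +0.010 to +0.020 | 0 | 0.000 |
| 0 | 4 | +0.020 to +0.040 | 0 | 0.000 |
| 1 | 2 | +0.010 to +0.020 | −2·0.05/17 = −0.006 | −0.006 |
| 1 | 4 | +0.020 to +0.040 | −4·0.05/17 = −0.012 | −0.011 |
| 2 | 2 | +0.010 to +0.020 | −2·0.10/20 = −0.010 | −0.010 |
| 2 | 4 | +0.020 to +0.040 | −4·0.10/20 = −0.020 | −0.020 to −0.021 |

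Without M, the simulation returns the truth in every case (for example, true +0.020, estimated +0.020).

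The first two rows need only that the benefit acts through sodium. The last four also need g > 0, meaning that patients with a better outlook correct more. If g were negative, the formula gives the same amounts with a plus sign. The Discussion notes that patients discharged quickly may not be fully corrected. If those patients are the healthier ones, the bias would run that way. The article does not fix the direction.

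**Scale.** With an assumed SD of 0.25 and about 94% of 2,050 patients scored, the standard error of the arm difference is 0.25·√(4/1,927) = 0.011. The assumed true effects are therefore about 0.9 to 3.5 standard errors. At the upper end, a detectable benefit would be lost.

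**The case against.** The strongest reply is that the wording is looser than the point makes it. The word also could mean a further analysis beside a plain arm comparison, the linear models are described as exploratory, and nothing says that an unadjusted comparison is left out. A model with correction reported beside an arm comparison would be acceptable. But the sentence is about the arm differences themselves, and neither score is in the list analysed like the primary outcome. As the text stands, the only stated arm comparison includes correction. The exploratory wording and the secondary status limit the consequence; they do not make the model answer the stated objective.

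It is also fair to say that the numbers are built on assumptions, and that a fully mediated effect goes to zero by construction. That concerns the size. The cancellation of b·Δ holds for any values.

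A reader might infer more from the qualifier in "Score of quality of life EQ-5D-5L Test (if applicable": that quality of life is compared only among survivors able to answer, which penalizes an arm that keeps frail patients alive. The article does not support this. The item stands in a list of survey questions, the same tag follows date of death, and a general practitioner may be the contact. No analysis set and no rule for deaths is stated, and a condensed article may leave both to the full protocol or the SAP. The size at 30 days is also small. Applying the planned relative reduction to the 6.4% mortality of the source study gives 6.4%·18/23 = 5.0%. The extra share of survivors is then (0.064 − 0.0501)/(1 − 0.0501) = 1.5%. At an assumed utility deficit of 0.2 to 0.6 in those patients, the shift is −0.003 to −0.009, below one standard error. Larger shifts at 1 year would need a mortality figure that the article does not give.

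**Conclusion.** Wrong as written, for secondary outcomes only. A between-arm model that contains achieved correction does not estimate the effect of allocation on quality of life or executive functioning. A benefit acting wholly through sodium is estimated as about zero: +0.010 to +0.040 becomes 0.000 under the assumed inputs. If only part of the benefit acts through sodium, that part is removed.

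A reader might go further and say that the planned model reverses the sign. That is possible but not shown by the documents. It needs an assumed shared prognostic factor working in the assumed direction, which gives −0.006 to −0.021 here. The firm conclusion is loss of the mediated effect plus a bias of unknown direction.

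The primary analysis, its conclusion and the sample size do not depend on this.

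**What to change.** State the between-arm model for both scores as score on arm, with baseline variables only: baseline grade of hyponatremia, for which the Subgroup Analyses categories would serve, and site, because randomization is stratified by it. Say explicitly that grade means the value at baseline and that achieved correction is not in this model.

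Report any model with achieved correction in a separate place, labelled as a non-randomized association analysis.

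The cost is two or three sentences and at most one more table, with no new data and no change in sample size. What is given up is a single model that speaks to both questions, and the separate report keeps that information. A supportive EQ-5D-5L table with deaths scored as zero could be added, since survival status and date of death are already collected. It is optional and mixes survival with quality of life.
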